Study Information

1. Title: Testing Active Interventions to Reduce Questionable Research Practices (2018)

2. Authorship: [name], [name], [name], [name] (order TBD)

3. Research Question:

This study will investigate whether research participants who receive an intervention designed to leverage “consistency” motives will indicate less support for various questionable research practices (QRPs) than participants in the control condition. The list of 15 QRPs to be used are a list of ambiguously unethical QRPs derived from previous work ([name], [name], & Brown, 2018). Regarding each of the 15 QRPs, participants will be asked the extent to which they find the behavior ethically defensible and the extent to which they would be willing to engage in the behavior. Both questions are to be answered using a 7-point Likert scale. Participants will be randomly assigned to one of two conditions on a between-participants basis: consistency motives activation or control condition. Participants will be instructed to engage in a specific writing task in each condition prior to completing the QRP endorsement questionnaire. All materials are appended below.

4. Hypotheses

Our primary hypothesis is that participants who receive the active consistency intervention will be less likely to find the QRPs ethically defensible and to express a willingness to engage in them.

Our secondary hypotheses, as suggested by our own previous findings, is that the impact of the consistency motives intervention relative to control will be more pronounced for 1) researchers with less experience and female researchers, compared to more experienced researchers and men.

We also intend to collect other demographic information, such as academic field/discipline, which we may use for exploratory analyses to inform subsequent research.

5. Sampling Plan

Data will be collected in Qualtrics on two samples of 100 participants each (N=200). This is based on a power analysis to detect medium-sized effects (Cohen’s d=0.4, β=0.80). One sample will consist of active NIH/NSF-funding researchers. Invitations will be sent out in waves, as in past use of this population ([name] et al., 2018), until 100 participants have been reached. The second sample will consist of 100 active researchers recruited from University of Mississippi Medical Center (UMMC) in Jackson by [name].

Participants will be given the option of receiving a $10 Amazon e-gift card in return for participation if they supply email addresses. The email addresses will be automatically de-linked from participants’ responses.

Stopping Rule: Total sample size of 200, which we determined to be sufficient through a power analysis. Responses will be checked daily and data collection will terminated in each sample once 100 participants have validly completed the study.

6. Variables

The key experimental manipulation is condition, consisting of the beginning reading prompt and writing task.

The measured outcome variable is the responses to the two questions (defensibility and willingness to engage) for each of the 15 QRPs.

The study is a no blinding experiment, randomizing participants in Qualtrics into either an experimental intervention (consistency) or control.

We will ensure scale reliability by computing Cronbach’s alpha prior to aggregating across QRPs, consistent with our past research. The omnibus statistical model will be a 2 Condition (Consistency Motives, Control) x 2 Participant Gender (Male, Female) custom ANCOVA, with participants’ years in their respective field as a continuous covariate. The custom model feature in SPSS will allow us to build interaction terms between categorical and continuous predictors, along with testing main effect predictions. If predicted statistical interactions between Condition and Participant Sex or Condition and Experience are significant, the former will be decomposed using simple effects analyses and the latter using simple slopes analyses. Additionally, we will compute and report effect sizes and confidence intervals to accompany the reporting of all analyses.

Below is the wording for the 2 instructions, consistency and control.

7. Materials

Consistency Condition Instructions:

Over the past few years, scientists have become increasingly aware of how various ethically questionable research practices can lead to poor science and reduce the ability of scientific research to improve human understanding and well-being.  Please begin by spending 3 – 5 minutes writing (in the box below) about how you attempt to model research integrity in your own work and with those you mentor, and how this commitment is consistent with your core ethical standards.

Control Condition Instructions:

Research misconduct, standardly defined, consists of falsification, fabrication and plagiarism (FFP). It can lead to poor science and reduce the ability of scientific research to improve human understanding and well-being. Please begin by spending 3 - 5 minutes writing (in the box below) about why falsification, fabrication and plagiarism are ethically objectionable.

QRP Questionnaire:

For each of the Questionable Research Practices below, participants will be asked:

To what extent is this behavior ethically defensible?

| Completely Indefensible | Moderately Indefensible | Somewhat Indefensible | Neither Defensible nor Indefensible | Somewhat Defensible | Moderately Defensible | Completely Defensible |
| --- | --- | --- | --- | --- | --- | --- |
| 1 | 2 | 3 | 4 | 5 | 6 | 7 |

To what extent would you be willing to engage in this behavior?

| Completely Unwilling to Engage in this Behavior | Moderately Unwilling to Engage in this Behavior | Somewhat Unwilling to Engage in this Behavior | Neither Willing nor Unwilling to Engage in this Behavior | Somewhat Willing to Engage in this Behavior | Moderately Willing to Engage in this Behavior | Completely Willing to Engage in this Behavior |
| --- | --- | --- | --- | --- | --- | --- |
| 1 | 2 | 3 | 4 | 5 | 6 | 7 |

QRPs:

1. To enhance chances of publication, violating the ideal of “replace, reduce, refine” regarding the use of research animals.

2. Adding additional research participants because the results collected thus far are not yet statistically significant.

3. Stopping collecting data earlier than planned because the hypothesized result already had been attained.

4. Rounding off a p value simply to make results seem more significant, such as by reporting a p value of .044 to be p = .04.

5. Deciding whether to include or exclude data after looking at the impact of doing so on the results.

6. Failing to report all of a study’s outcome measures.

7. Selectively discussing only studies that supported the hypothesized result(s).

8. Reporting an unexpected result as having been hypothesized from the start.

9. Drawing strong inferences from statistically significant but underpowered results.

10. Selective reporting of subgroups, outcomes, and time points.

11. Deliberately delaying reporting results in order to publish findings in a higher impact journal.

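### The primary hypothesis needs an effect on both outcomes, but the stated 80% power fits a test of only one; for both it is about 0.69 to 0.77

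*Protocol*

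**What the plan says.** The primary hypothesis (protocol, section 4) is that the intervention group "will be less likely to find the QRPs ethically defensible and to express a willingness to engage in them". Section 6 describes the outcome in the singular but includes both questions: "The measured outcome variable is the responses to the two questions (defensibility and willingness to engage) for each of the 15 QRPs". The questionnaire in section 7 gives each question its own 7-point scale with its own anchors.

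On scoring, section 6 says "We will ensure scale reliability by computing Cronbach’s alpha prior to aggregating across QRPs, consistent with our past research". This is aggregation over the 15 items. Nothing says whether the two questions are then merged or kept apart. One ANCOVA model is described, without saying whether it is run once or once per question.

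On sample size, section 5 says "Data will be collected in Qualtrics on two samples of 100 participants each (N=200" and gives the basis as a "power analysis to detect medium-sized effects (Cohen’s d=0.4, β=0.80". The stopping rule repeats the claim: "Total sample size of 200, which we determined to be sufficient through a power analysis". On allocation, section 3 says only "Participants will be randomly assigned to one of two conditions on a between-participants basis: consistency motives activation or control condition", with no ratio. The protocol states no significance level, no sidedness, and no rule for whether both outcomes or either one decides the primary hypothesis.

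**The concern.** The hypothesis and the power statement appear to describe different claims. One asks for an effect on defensibility and on willingness; the other is sized for one comparison of two means. Power to win on both of two imperfectly correlated outcomes is always below the power to win on one, so the 80% does not carry over to the hypothesis as worded.

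The missing decision rule makes this matter in practice. If one score reaches significance and the other does not, the protocol does not say whether the primary hypothesis is supported, and the choice could be made after seeing the data. Section 7, item 10 of the study's own questionnaire lists selective reporting of outcomes as a questionable practice, so the primary claim should not leave that choice open.

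**Working it through.** **Inputs.** From the protocol: d = 0.4; 0.80, printed as β but read as power because that reading reproduces N; N = 200. Assumed: 100 per condition (1:1), two-sided 5%, d = 0.4 on both composites, and a correlation r between the two scores within condition. The documents give no value for r, so it is shown as a range.

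**1. Reproducing N = 200.** Per condition, n = 2(z₀.₉₇₅ + z₀.₈₀)²/d² = 2(1.960 + 0.842)²/0.16 = 98.1, so 99 (198 in total). The noncentral t gives 100 per condition, 200 in total, an exact match. A one-sided 5% test gives 2(1.645 + 0.842)²/0.16 = 77.3, so 78 per condition (156 in total), which does not match. The stated N is therefore that of one two-sided 5% test of one outcome.

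**2. Power for one outcome.** The noncentrality is 0.4 × √(100/2) = 2.828. The normal approximation gives Φ(2.828 − 1.960) = 0.807; the noncentral t gives 0.804.

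**3. Power for both.** This is Φ₂(s, s; r), the bivariate normal probability that both tests are significant in the predicted direction, with s chosen so that each margin equals 0.804. At r = 0 it is 0.804² = 0.646. Using 0.807 for the margin instead raises each value by about 0.004 to 0.006.

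**4. Chance of a split result.** This is 2 × (0.804 − joint power). At r = 0.7, for example, 2 × (0.804 − 0.718) = 0.17.

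**5. Type I error if either score sufficed without adjustment.** This is 1 − P(|Z₁| ≤ 1.96 and |Z₂| ≤ 1.96). At r = 0 it is 1 − 0.95² = 0.0975.

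**6. Total N for 80% power on both** (normal approximation).

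| r | Power for both, N = 200 | Split result | Type I error, unadjusted either-rule | N for 80% on both |
| --- | --- | --- | --- | --- |
| 0 | 0.65 | 0.32 | 0.0975 | 258 |
| 0.5 | 0.69 | 0.22 | 0.091 | 246 |
| 0.7 | 0.72 | 0.17 | 0.084 | 236 |
| 0.9 | 0.75 | 0.10 | 0.070 | 220 |
| 0.95 | 0.77 | 0.07 | 0.065 | 214 |

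The power and type I columns belong to different decision rules. Requiring both keeps the error at or below 5% and loses power; accepting either one unadjusted keeps power at or above 80% and inflates the error.

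**7. Covariate gain that would close the gap.** If d = 0.4 is on the unadjusted scale, gender and years in field would need to explain about 1 − 200/N of the residual variance: 1 − 200/220 = 9% at r = 0.9, 1 − 200/236 = 15% at r = 0.7, and 1 − 200/258 = 22% at r = 0.

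**The case against.** The strongest reply is that the protocol may intend one outcome. Section 6 uses the singular and describes one model, and section 3 speaks generally of support for the practices. A single combined endorsement score would deliver both 80% power and a 5% error rate, if d = 0.4 refers to that score. The text does not exclude this. However, the only aggregation described is over the practices, and the hypothesis names the two responses separately, so two composites is the more natural reading.

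Second, two ratings by the same person on the same items are probably positively correlated, which makes the r = 0 row a worst case, and the ANCOVA covariates may recover some power. Both points are fair. They narrow the gap, but the protocol quantifies neither.

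Third, the commitment to report effect sizes and confidence intervals for all analyses makes a split result harder to conceal. That is true, but it does not supply a decision rule.

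Stronger readings are tempting and should be resisted:

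- A reader might infer that each score gets an unadjusted 5% test. The protocol does not say so: the 5% is only deduced from N = 200, and an adjustment may sit in a statistical analysis plan that is not shown.
- A reader might infer that either the 80% or the 5% must fail. A combined score escapes that. So does an either-rule with Bonferroni (0.025 each), which keeps the error at or below 5% and power for at least one score at or above 80% up to about r = 0.8 (0.807 there, 0.782 at r = 0.9).
- A reader might extend the point to the interaction tests. Those are secondary hypotheses, and adjusting across them is a choice that an analysis plan may settle.

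**Conclusion.** The concern holds in a limited form. As worded, the primary hypothesis asks for an effect on both outcomes, while N = 200 gives the stated 0.80 for one outcome only. On two composites, both required, power is about 0.69 to 0.77 for r from 0.5 to 0.95, a shortfall of roughly 3 to 11 percentage points against 0.80. This rests on 1:1 allocation, a two-sided 5% level, d = 0.4 on both scores and no covariate gain. A smaller effect on either score would lower the joint power further.

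The more consequential part is the open decision rule, since a split result is a realistic outcome and could be read either way. This should be fixed, but it does not undermine the design: requiring both causes no type I error problem, and the remedy is one of wording.

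**What to change.** Before any data are examined, state in section 4 that the primary hypothesis is supported only if the Condition effect is significant at two-sided 0.05, in the predicted direction, on both 15-item composites. In section 5, replace 0.80 with power for that claim, about 0.70 to 0.75, and name the assumed correlation, allocation ratio and significance level.

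If support from one score alone is meant to count, say so and apply Holm across the two scores: the smaller p-value is tested at 0.025 and, if that is significant, the other at 0.05. If a single combined score was intended, define it.

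The cost is a few sentences and either a less favourable power figure or a stricter first threshold. No extra participants are needed. Keeping 80% power for both scores is optional and would take about 214 to 258 participants in total, depending on the correlation.

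### The primary Condition test shares a model with the Condition x years interaction and no centring is stated; with raw years it would estimate the effect at zero years in the field, not the average effect

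*Protocol*

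**What the plan says.** Protocol section 4 states the primary hypothesis for participants as a whole: "Our primary hypothesis is that participants who receive the active consistency intervention will be less likely to find the QRPs ethically defensible" (and less willing to engage in them). The secondary hypothesis is that the effect "will be more pronounced for 1) researchers with less experience and female researchers, compared to more experienced researchers and men".

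Section 5 sets the sample size: "Data will be collected in Qualtrics on two samples of 100 participants each (N=200", from a "power analysis to detect medium-sized effects (Cohen’s d=0.4, β=0.80". The 0.80 is evidently meant as power.

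Section 6 gives a single omnibus model, a Condition by Gender custom ANCOVA "with participants’ years in their respective field as a continuous covariate". On what the model is for, it says: "The custom model feature in SPSS will allow us to build interaction terms between categorical and continuous predictors, along with testing main effect predictions". A significant Condition by Experience interaction is to be followed by simple slopes. The demographic items in section 7 collect experience as a plain number of years.

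The protocol does not say whether years are centred, at what value of years the Condition effect is evaluated, or whether Condition is also tested without the interactions.

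**The concern.** When a model contains a Condition x years product, the Condition term is no longer an average over participants. It is the difference between arms where the years variable equals zero. If years are entered as collected, that point is a researcher with no time in the field. The primary test then answers a different question from the primary hypothesis, and the power calculation no longer describes it.

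There are two possible consequences. If experience does not modify the effect, the contrast at zero is estimated much less precisely than the average, and power falls. If the effect is larger in less experienced researchers, as the protocol predicts, the contrast at zero is larger than the average, and the result would overstate the overall effect.

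**Working it through.** **Inputs from the protocol.** d = 0.4, power 0.80 and N = 200 (section 5); two randomised conditions (section 3); one model with Condition, gender, years and interactions (section 6).

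**Assumptions.** 1:1 allocation (100 per condition), two-sided alpha 0.05, outcome in SD units. The mean M and SD S of years are not given, so the ratio r = M/S is varied from 1 to 2.

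**Step 1: the plan's own figure.** A two-group comparison at d = 0.4 and 80% power needs 99 per condition, 198 in total, which agrees with 200. With 100 per condition, power is 0.804 (noncentral t, 198 df). The stated size therefore matches a plain comparison of arms, that is, the average effect.

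**Step 2: what the Condition term estimates.** Write the effect of Condition at years x as δ(x) = δ̄ − k(x − M)/S, where δ̄ is the average effect and k is its fall per SD of years. With centred years the Condition term estimates δ̄. With raw years it estimates δ(0) = δ̄ + k·r.

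**Step 3: its precision.** For the average effect, SE² = 4/200 = 0.02, so SE = 0.141. For the contrast at zero years, SE² = 0.02 × (1 + r²).

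- r = 1: SE = √(0.02 × 2) = 0.200
- r = 1.5: SE = √(0.02 × 3.25) = 0.255
- r = 2: SE = √(0.02 × 5) = 0.316

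**Step 4: power with raw years** (noncentral t, 194 df, δ̄ = 0.4).

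| r | k = 0: effect at zero | power | k = 0.2: effect at zero | power |
|---|---|---|---|---|
| 1 | 0.40 | 0.51 | 0.60 | 0.85 |
| 1.5 | 0.40 | 0.35 | 0.70 | 0.78 |
| 2 | 0.40 | 0.24 | 0.80 | 0.71 |

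With centred years in the same model, power is 0.80 if the genders are balanced. With an assumed 40% women it is about 0.79, because the Condition term then weights the genders equally: SE² is multiplied by 1/(4 × 0.4 × 0.6) = 1.04.

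**Step 5: simulation** (gamma-distributed years, mean/SD from 8/8 to 20/10).

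- Constant effect of 0.4: power with raw years 0.50, 0.40, 0.33 and 0.24 at ratios 1, 1.25, 1.5 and 2; about 0.78 with centred years; about 0.80 without interactions.
- Fall of 0.2 per SD of years: power with raw years 0.70 to 0.83, and the Condition estimate averages 0.61 to 0.81 against a true average of 0.40.

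**Step 6: when power is not lost.** The raw test matches the centred one when 0.4 + k·r = 0.4·√(1 + r²), that is, k = 0.4(√(1 + r²) − 1)/r. This gives k = 0.17, 0.21 and 0.25 at r = 1, 1.5 and 2. If the effect falls more steeply than this, the raw test has more power, but for the effect at zero years.

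**The case against.** The strongest objection is that the protocol never says years will be left uncentred. Coding of covariates is often left to an analysis plan, and the planned simple slopes already require someone to choose values of years. This stands in part: the point has to be conditional. It does not dispose of the point, because section 6 itself fixes the software, the model, the covariate and the joint testing of main effects and interactions. It also describes a preparatory step (scale reliability) and the follow-up tests. Run as written on the variable as collected, the model tests the arms at zero years.

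A reader might also infer that most of the 80% power is lost. The documents do not support that. Losing more than half needs a roughly constant effect and a mean/SD ratio above about 1.3, and neither is documented. Under the protocol's own secondary hypothesis, power may fall little or even rise.

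A reader might further infer that zero years lies far outside the data because the participants are established, funded researchers. Only one of the two samples is defined by NIH/NSF funding. The other is active researchers at one medical centre, and no minimum experience is set. Under an assumed gamma distribution with mean 10 and SD 8, about 10% would have under 2 years. Zero is the edge of the data, not demonstrably beyond it.

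Finally, if the average effect were exactly zero but the effect fell by 0.2 per SD of years, the raw test would reject about 17% to 24% of the time for ratios of 1 to 2 (step 3's SE, effect at zero of 0.2 to 0.4). A reader might call this type I error inflation. It is a correct rejection about a different quantity, so it is a problem of interpretation.

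**Conclusion.** The point holds in conditional form. Section 6 puts the primary Condition test in a model whose Condition term depends on where the years variable has its zero, and does not say where that is. Entered as collected, years make the primary test a contrast at zero experience instead of the average effect in section 4.

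The mismatch in what is estimated follows from the model alone. Its size rests on assumptions about the distribution of years and the degree of moderation. Either the effect is constant and precision is lost, or it falls with experience as predicted and the main effect is overstated by roughly half to double (0.6 to 0.8 against 0.4). Centring, or a model without interactions, avoids both.

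**What to change.** Add two sentences to section 6, in one of two forms:

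- Test the primary Condition effect in a model with Condition, gender and years and no interaction terms. Test Condition x Gender and Condition x years in a second model.
- Or keep the single model, centre years at the pooled sample mean before forming the product, and state that the Condition effect is the effect at mean years.

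Either form keeps power at about 0.78 to 0.80 for d = 0.4. The cost is a text change made before analysis; recruitment, data collection and sample size are unaffected. Whether to add a term for the two recruitment samples is a separate question and not part of this change.
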